**Table Tabb:** 

		Enrolment			Post-allocation		Close-out
			After consent	After randomisation	Treatment	14 weeks after randomisation	26 weeks after randomisation
Timepoint:			Baseline			Post-treatment	Follow-up
Enrolment	Eligibility screen	X					
	Informed consent	X					
	Allocation			X			
	Demographic information		X				
Interventions	OSI				X		
	C-TAU				X		
Assessments							
Child report							
Symptom measure	RCADS-C		X			X	X
Functional impairment	CAIS-C		X			X	X
Adverse Events	AE Self-report					X	X
Parent report							
Symptom measures	RCADS-P		X			X	X
	SCAS-P-8		X			X	X
Functional impairment	CAIS-P		X			X	X
	ORS		X			X	X
Co-morbid problems	SDQ-P		X			X	X
Pandemic Anxiety Scale	PAS		X			X	X
Treatment acceptability	Credibility and Expectation of Improvement scale			X		X	
Adverse events	AE Self-report					X	X
Health economics	CSRI		X			X	X
	EQ-5D-5L- P		X			X	X
	CHU-9D (YP proxy)		X			X	X
	CAIS-P		X			X	X
OSI+therapist support ARM ONLY Measures collected during treatment (parent only)	RCADS-P				X		
	SCAS-P-8				X		
	CAIS-P				X		
	ORS				X		
	SRS				X		
	GBOs				X		
Qualitative interviews						X (subgroup of participants interviewed once each between 14 and 26 weeks).	
Therapist Logs					X	X	X

### Sample size {14}

Between 418 and 560 children (209–280 per group) with a primary anxiety problem and their parents will be randomised across the two treatment arms. This sample size is considered to be sufficient to provide a standardised noninferiority margin = 0.33 and between 80 and 90% power (allowing for 30% attrition). The required sample size was calculated using PASS 2019.

A sub-sample of up to 20–40 parents and therapists/supervisors from both arms will be involved in qualitative interviews to explore their experiences of treatment. We will purposively sample from parents who have reached 14 weeks post-randomisation until we reach saturation in terms of (i) representation across the sample for geographic, economic, and educational backgrounds and (ii) until no new themes are identified. We will also aim to recruit therapists who reflect differing characteristics (e.g. service provider type and location, demographic factors, and clinical backgrounds), as well as therapists’ supervisors. We have previously found that this number of participants is typically sufficient for data saturation.

### Recruitment {15}

Participating families will be identified by their clinical teams. Clinical teams will follow their usual procedures to identify the child’s primary presenting problem. The clinical team will conduct an initial assessment of eligibility according to the inclusion and exclusion criteria. Where the clinical team identifies that the study inclusion criteria are met (and exclusion criteria are not), they will briefly outline the study to the parents. If parents express an interest in the study, they will be asked to provide an email address to which they will be sent a secured link to the study IT system where the parent will be able to access online information sheets which will provide further information about the study and what would be expected of the participants, alongside contact details for the study team (email and phone number) so that they can be contacted to answer any questions. There will also be video information (information sheet text being read aloud verbatim). In addition, there is dedicated, age-appropriate, online information including a video (consisting of the information sheet with text being read aloud verbatim) for the child. The parent will then be invited to provide online consent for themselves and their child. Where parents provide consent, a further email will be sent with a link for the child to provide assent.

Therapists whose role includes delivery of psychological interventions to children with anxiety problems within participating clinical teams will be invited to take part and consenting families will be allocated to these therapists for treatment. Allocation of families to therapists will be managed within participating clinical teams.

## Assignment of interventions: allocation

### Sequence generation {16a}

Participants will be randomised in a 1:1 ratio to (i) OSI+therapist support or (ii) CAMHS treatment as usual for child anxiety problems within the COVID-19 context (C-TAU).

Minimisation by child age (≤8; ≥9), gender, service type (school based or not school based), and baseline anxiety-associated interference including permuted block size will be used to ensure balance across groups.

### Concealment mechanism {16b}

Participants will be randomised using a fully validated and secured web-based randomisation system called Sortition that will automatically occur after the participating parent completes the consent and baseline measures, and the child completes assent (online).

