### Who will take informed consent? {26a}

Parents will provide online consent for themselves and their child, and children will provide online assent via a secure online system.

Although the child may choose not to provide any data directly (if they do not wish to complete any of the child report measures), both parent consent and child assent are required for randomisation. We anticipate that some participating children will need adult support to understand the study information and assent and to complete the measures and we will provide parents with guidance on how to do this with instructions available on the online system.

Participant information (parent/child/therapist) will be provided in written and video form (for parents and children) providing information on the exact nature of the study; what it will involve for the participant; the implications and constraints of the protocol; and the known side effects and any risks involved in taking part. It will be clearly stated that the participant is free to withdraw from the study at any time for any reason without prejudice to future care, without affecting their legal rights, and with no obligation to give the reason for withdrawal. Each potential participant will be given sufficient time to read through the participant information sheet and ask questions, either to the clinical contact or the research team, before deciding whether to take part.

If clinical teams have not been notified that a participating family has consented/assented to the study within 2 weeks of approach, they will be free to contact the participant to arrange alternative treatment. Clinical teams will be notified 2 weeks before the overall study recruitment window is coming to an end so that they can inform any families that have not yet responded how much time they have left to consent/assent should they wish to participate.

Participants must provide their name and date of the latest approved version of the informed consent form (via a unique link) before any study-specific procedures are performed. A copy of the signed informed consent/assent forms will be available to be downloaded at each timepoint when the parent accesses the system and notice of this will also be emailed to the local investigator (or their delegated authority), who will also have access to download these from the system to add them to the child’s medical record.

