#### Secondary measures and objectives

*Secondary clinical outcomes*: Child-reported anxiety interference (CAIS-C) and anxiety symptoms (RCADS-C). Parent-reported child anxiety symptoms (RCADS-P, SCAS-8P), overall functioning (ORS), COVID-19-specific worries, and common comorbid emotional and behavioural problems (SDQ-P). All will be measured at 14 and 26 weeks post-randomisation.

*Secondary clinical objective:* Further assessment of the clinical effectiveness of OSI+therapist support for the treatment of child anxiety compared to COVID-19 treatment as usual (C-TAU) in CAMHS throughout the next phases of the COVID-19 pandemic.

*Economic outcomes*: Parent quality of life (EQ-5D-5L, parent-self report); child quality of life (CHU-9D proxy version, i.e. parent-report on child); and the Child Anxiety Impact Scale- parent report (CAIS-P). School attendance (parent-reported actual school attendance as a percentage of expected school attendance). Therapist logs of time spent on treatment delivery. Measured at 14 and 26 weeks post-randomisation.

*Economic objective*: To evaluate the cost-effectiveness of OSI+therapist support for the treatment of child anxiety compared to COVID-19 treatment as usual (C-TAU) in CAMHS.

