### Participant timeline {13}

Where parents and their children provide online consent or assent, respectively, they will be asked to complete online baseline assessments (all questionnaires), prior to randomisation. After randomisation, parents will be asked to complete a further short questionnaire about treatment expectations and acceptability. Treatment in both arms will be organised by the clinical teams who will be requested to start as soon as possible and at most within 12 weeks of randomisation. Families allocated to the intervention arm will access OSI and a member of the clinical team will provide support as they work through each OSI module. Participating parents and children in both arms (OSI+therapist support and C-TAU) will be sent a link to complete post-treatment and follow-up assessments (questionnaires) online 14 and 26 weeks after randomisation.

Therapists will provide information on COVID-19 treatment as usual for each participant at the start of their treatment within the therapist treatment logs in order for us to be able to describe what services are delivered in the COVID-19 context, specifically the treatment approach being followed, who they are having contact with (e.g. child, parent, both), and for how long.

Therapists will provide brief demographic information at the study outset, will record information on activity with each participating family, and will complete a brief questionnaire about their experience of the treatment after completing treatment with each participating family.

We will also conduct qualitative interviews with a subgroup of parents and therapists/supervisors (*n*= 25–40), between 14 and 26 weeks after randomisation, purposively sampled on the basis of demographics, and we will continue to sample to ensure variability in treatment outcomes across both arms, if possible, to explore and to understand therapist and parents’ experiences of treating child anxiety in this context.

SPIRIT schedule of enrolment, interventions, and assessments

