### Implementation {16c}

Sortition will automatically send an email, including the result of the allocation treatment arm, to the trial team, the clinical team, and the participants.

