## Data collection and management

### Plans for assessment and collection of outcomes {18a}

Assessments will be completed via online self-report questionnaires, administered at baseline, 14 weeks post-randomisation (post-treatment) and 26 weeks post-randomisation (follow-up). The research team will keep careful track of assessment completion and will contact participants (by email, text, phone) if measures have not been completed within 3 days of the invitation to encourage completion of measures (at all timepoints).

A summary of the measures that are provided at each timepoint is given in the ‘Participant timeline {13} section.

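### The automatic randomisation trigger omits the child's baseline forms, so it does not guarantee the order that the timeline states for CAIS-C and RCADS-C

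*Protocol article*

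**What the plan says.** **Intended order.** Participant timeline {13} states that once parents have consented and children assented, "they will be asked to complete online baseline assessments (all questionnaires), prior to randomisation". The schedule in that section agrees. RCADS-C and CAIS-C stand in the baseline column after consent, and the only assessment in the column after randomisation is the credibility and expectation scale.

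**Operating rule.** Under Concealment mechanism {16b}, randomisation will "automatically occur after the participating parent completes the consent and baseline measures, and the child completes assent (online"). That is three conditions: parent consent, parent baseline and child assent. Who will take informed consent? {26a} is consistent with this. It begins "Although the child may choose not to provide any data directly (if they do not wish to complete any of the child report measures") and adds that "both parent consent and child assent are required for randomisation".

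**Disclosure and reminders.** Implementation {16c} says that "Sortition will automatically send an email, including the result of the allocation treatment arm, to the trial team, the clinical team, and the participants". Who will be blinded {17a} confirms that families cannot be blinded. Under Plans for assessment and collection of outcomes {18a}, the team contacts participants "if measures have not been completed within 3 days of the invitation to encourage completion of measures (at all timepoints").

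**Use of the score.** Analysis of clinical outcomes puts the baseline score in the mixed model as a fixed effect and extends a similar approach to the secondary outcomes. These include "Child-reported anxiety interference (CAIS-C) and anxiety symptoms (RCADS-C").

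**The concern.** Adjusting for a baseline score is safe because the score is fixed before allocation and so cannot depend on the arm. A score given after the family has learned its allocation loses that protection: relief or disappointment at the arm may colour the answers. Section {26a} also expects that some children will need adult help with the measures, so a parent's reaction could reach the child's form.

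CAIS-C and RCADS-C are the only clinical outcomes in the protocol that the child rates. All the others come from the parent, who knows the arm. These two are therefore the natural cross-check on the parent-reported results, and their baseline should be beyond question.

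**Working it through.** The protocol gives no figure on this point. The main check is of event order.

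**1. Conditions against intention**

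| Step | Before randomisation per {13} and schedule | Condition of the trigger per {16b} |
|---|---|---|
| Parent consent | yes | yes |
| Parent baseline, including CAIS-P | yes | yes |
| Child assent | yes | yes |
| Child baseline, CAIS-C and RCADS-C | yes | not listed |

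**2. Which sequences does the trigger allow?** Recruitment {15} sends the child's assent link only after the parent has consented. Section {26a} requires consent procedures before any study-specific procedure, so the child's forms follow assent.

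- *Parent baseline finishes last.* The child may assent and complete the forms while the parent is still working. The intended order can hold.
- *Child assent finishes last.* All three conditions are met at the moment of assent. Read literally, randomisation occurs before the child can have completed a form.
- *Child declines the forms.* Randomisation proceeds and the child baseline is missing. This is what {26a} allows and is no problem.

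The rule as written cannot tell a child who declines from one who has not yet filled in the form. The reminder rule covers all timepoints and does not separate them either.

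**3. Which outcomes are exposed?** The CAIS-P baseline belongs to the parent's measures, which {16b} requires before randomisation. The same holds for the other parent-reported outcomes. Only CAIS-C and RCADS-C are exposed.

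**4. Possible size, on assumed inputs.** In SD units, the adjusted effect is approximately

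(difference in outcome means) − b × (difference in baseline means),

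where b is the baseline slope. Suppose a share f₁ of the OSI arm and f₀ of the C-TAU arm complete late, with mean shifts d₁ and d₀. Then

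bias ≈ −b × (f₁d₁ − f₀d₀).

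Equal shares with equal shifts give zero. With a common share f and a net between-arm shift δ = d₁ − d₀, the absolute bias is b × f × δ. None of b, f or δ is in the protocol, so each is an assumption:

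| b | f | δ (SD) | b × f × δ (SD) |
|---|---|---|---|
| 0.4 | 0.10 | 0.1 | 0.004 |
| 0.5 | 0.05 | 0.2 | 0.005 |
| 0.5 | 0.25 | 0.4 | 0.050 |
| 0.7 | 0.50 | 0.3 | 0.105 |

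For scale, a share of 5% to 25% is 21 to 105 children of 418, or 28 to 140 of 560. The direction of any bias is unknown.

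**The case against.** The strongest reply is that the plan's intended order is right and is stated twice, in the timeline text and in the schedule. Nowhere does the protocol plan or describe a child baseline completed after allocation. The sentence in {16b} is condensed, and {26a} offers a good reason for leaving the child's measures out of it: a child may decline them all and still be randomised. On that reading a non-responding child has a missing baseline, not a contaminated one. Late completion also needs the child's form to stay open after randomisation, and no section says that it does. Closure of forms could well be settled in the Data Management Plan or the SAP, which are not shown.

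Most of this stands. A reader might infer that child baselines are in fact collected after families know their arm and are then used for adjustment. The documents do not support that: they show an order that the trigger fails to secure, not one that is breached. A reader might also set the assumed bias against the 0.33 margin, where 0.05/0.33 is about 15%. That figure multiplies unfavourable assumptions together, treats the shift as a net difference between arms, and borrows a margin given in the sample size section for outcomes that are only secondary.

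What does not fall away is the mismatch itself. The trigger is automatic, so its listed conditions decide the order. Those conditions differ from the order stated in {13}, so this is more than detail left to another document.

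**Conclusion.** The point holds as a minor inconsistency. As written, {16b} does not guarantee that CAIS-C and RCADS-C baselines precede knowledge of the arm, although {13} says that they do. The gap is clearest when the child's assent is the last step. A score obtained after allocation could then enter the model as a baseline covariate for these two outcomes.

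The effect is confined to two secondary outcomes, and the primary CAIS-P comparison is untouched. Neither the number of late child baselines nor their effect can be known from the protocol. The range of 0.004 to 0.105 SD rests wholly on assumed slopes, shares and net shifts, and it is zero if the share late and the shift are the same in both arms or if no child form was accepted after randomisation.

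**What to change.** **Text.** Reconcile {13} and {16b} by stating that randomisation requires the child's baseline form to be submitted or marked as declined. This keeps the child's right under {26a} to give no data. The cost is one workflow condition and a short delay for some families. Trial status gives 03/08/2022 as the end of recruitment, so for this trial the change only corrects the record or serves later use of the system.

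**Analysis.** Before the data are analysed by arm:

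1. Compare each child form's stamp with the randomisation time. Data recording and record keeping says that all forms are date stamped on receipt. If only dates are kept, the order of same-day forms needs a system log or a stated convention.
2. Report how many child baselines are late, by arm. If there are none, the matter is closed.
3. In the CAIS-C and RCADS-C models, treat any child baseline stamped after allocation as missing, for example by mean imputation of the baseline, and keep the child in the model.

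The cost is one time-stamp comparison and a slight loss of precision for the children whose baseline is set aside.

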### Implementation {16c}

Sortition will automatically send an email, including the result of the allocation treatment arm, to the trial team, the clinical team, and the participants.

## Assignment of interventions: blinding

### Who will be blinded {17a}

Due to the nature of the trial, blinding to condition is not possible to the trial participants or research team; however, the statistical analyses will be conducted blind to trial condition.

### Procedure for unblinding if needed {17b}

There are no planned interim analyses so unblinding of statisticians is not anticipated prior to the datalock.

## Data collection and management

### Plans for assessment and collection of outcomes {18a}

Assessments will be completed via online self-report questionnaires, administered at baseline, 14 weeks post-randomisation (post-treatment) and 26 weeks post-randomisation (follow-up). The research team will keep careful track of assessment completion and will contact participants (by email, text, phone) if measures have not been completed within 3 days of the invitation to encourage completion of measures (at all timepoints).

A summary of the measures that are provided at each timepoint is given in the ‘Participant timeline {13} section.

#### Demographic information

Participating child and parent demographics will be collected based on parent report. The data collected will include (i) parent age and child date of birth, (ii) parent and child gender, (iii) parent and child ethnicity, (iv) child use of medication, (v) parental education, (vi) parental employment status and occupation, (vii) household circumstances, (viii) employment and income details, and (ix) child’s school type and education provision. This information will be used to describe the sample, inform randomisation minimisation, and inform the health economic evaluation.

In order to describe therapists who delivered the treatment in this study, therapists will provide information on (i) their age, (ii) gender, (iii) ethnicity, (iv) professional background, (v) years qualified and of clinical experience, (vi) current working arrangements, (vii) experience of working with children with anxiety problems, (viii) relevant training, and (ix) preferred ways of working with children with anxiety problems and their families.

#### Impact of child anxiety

The Child Anxiety Impact Scale- parent report (CAIS-P/C): The CAIS-P/C will be used to determine the extent to which anxiety interferes with the child’s life. This measure covers three psychosocial domains (academic, social activities, and home/family environments) and consists of 27 items rated on a 4-point scale. An additional 4 ‘global’ items assess overall interference. There are versions for children and parents to complete, both of which have been shown to have good psychometric properties [21, 22]. The CAIS-P/C will be completed at baseline and then at 14 and 26 weeks post-randomisation by both parent and child.

#### Symptoms of child anxiety

Revised Child Anxiety and Depression Scale-Child and Parent version (RCADS-C/P): The RCADS-C/P is routinely used within CAMHS. It is a 47-item questionnaire, with corresponding child-report and parent-report versions that assess symptoms of separation anxiety disorder, social anxiety disorder, generalised anxiety disorder, panic disorder, obsessive compulsive disorder, and major depressive disorder. Responders rate how often each item applies on a 0 (‘never’) to 3 (‘always’) scale. The RCADS-C/P has been shown to have robust psychometric properties in children from age 7 [23, 24]. RCADS-C/P will be completed at baseline, and then at 14 and 26 weeks post-randomisation by both parent and child.

Brief Spence Children’s Anxiety Scale-Parent Version (SCAS-P-8): The SCAS-P-8 is a brief version of the Spence Children’s Anxiety Scale [25]. It is an 8-item questionnaire designed to assess symptoms of anxiety disorders in children. An initial evaluation of the questionnaire indicates it has good psychometric properties in children from ages 7 to 11 [25]. Only 1 of the 8 items is required to be collected to score this measure as 7/8 items overlap with those already collected within the RCADS-P. The additional item that enables us to calculate a SCAS-P-8 total score will be completed at baseline and then at 14 and 26 weeks post-randomisation by the parent and is added as an additional item at the end of the RCADS-P questionnaire.

